## Background

The incidence of pancreatic cancer has risen consistently from 1992 to 2020, while the number of deaths due to pancreatic cancer in the United States has also risen proportionately [1]. There will be an estimated 57,600 patients initially diagnosed pancreatic cancer in 2020, representing 3.2% of all new cancer cases. A total of 47,050 deaths due to pancreatic cancer are projected to occur in the U.S. in 2020 representing 7.8% of all cancer deaths [1]. Median overall 5-year survival for patients with Stage 1 and 2 pancreatic cancer has been reported to be 24.4 months while locally advanced pancreatic Stage 3 cancer (LAPC) has a median survival of less 1 year [2, 3]. Patients with Stage 3 pancreatic ductal adenocarcinoma (PDAC) represent 39.2% of the nonmetastatic patient population with an associated 5-year survival of 10.8% [2]. The probability of survival is inversely proportional to tumor size and the number of positive lymph nodes [4].

The current standard of care (SOC) for stage 3 PDAC includes systemic chemotherapy. FOLFIRINOX (combination chemotherapy using 5-fluorouracil [5-FU], leucovorin [folinic acid], irinotecan, and oxaliplatin) has demonstrated improved overall survival to 11.1 months for FOLFIRINOX versus 6.4 months for gemcitabine in metastatic pancreatic cancer, but at the cost of greater toxicity [5]. More recently, a modified form of FOLFIRINOX (without the bolus 5-FU and with a reduced dose of irinotecan) has been shown to have an acceptable safety profile while maintaining comparable efficacy of FOLFIRINOX in metastatic pancreatic cancer [6]. The National Cooperative Cancer Network (NCCN) has recently added modified FOLFIRINOX (mFOLFIRINOX) as a preferred regimen for Stage 3 pancreatic cancer patients with a good performance status (ECOG 0–1) [7].

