A growing body of evidence exists on the use of the NanoKnife System to treat pancreatic tumors, including both borderline resectable and unresectable tumors [14–16]. Studies have reported a median OS from diagnosis ranging from 14 to 27 months [17–27] and a median OS from IRE treatment ranging from 10 to 27 months [28–30]. The largest of these studies, a 200-patient, multicenter registry of patients with stage 3 pancreatic cancer treated with IRE via an open surgical approach, reported a median OS of 24.9 months and a median local progression free interval of 10.7 months [21]. Holland et al. recently reported results from a multicenter registry which included 152 patients with LAPC treated with IRE via an open approach at 6 different institutions [31]. Median OS from diagnosis, progression-free survival (PFS), and time to progression (TTP), all from diagnosis were 30.7 months, 22.8 months, and 27.3 months, respectively.

Narayanan et al. reported a retrospective review of 50 patients with LAPC treated with percutaneous IRE (26). Median OS was 27 months (95% confidence interval [CI], 22.7–32.5 months from the time of diagnosis) and 14.2 months (95% CI, 9.7–16.2 months) from the time of IRE. Multivariate analysis demonstrated patients with tumors ≤3 cm had significantly longer median OS than patients with tumors > 3 cm (33.8 vs. 22.7 months from time of diagnosis; *p* = 0.002, and 16.2 vs. 9.9 months from time of IRE; *p* = 0.031). More recently, Ruarus et al. reported the results of the Phase II multicenter PANFIRE II study which prospectively enrolled 50 patients treated with CT-guided percutaneous IRE [25]. This included 40 patients with LAPC and 10 patients with local recurring pancreatic cancer following resection. The median OS from diagnosis for patients with LAPC was 17 months. For patients with local recurrence, the median OS was 16 months from the diagnosis of recurrence and 9 months from IRE treatment. He et al. retrospectively compared 36 patients treated with IRE and 40 patients receiving radiotherapy with both groups receiving 4 months of induction chemotherapy prior to treatment [32]. Following a Propensity Score Matching (PSM) analysis, patients in the IRE group had longer median OS than patients receiving radiotherapy (21.6 months vs. 10.6 months) with significantly greater 1-year (71.4% vs. 41.3%) and 2 year (53.5% vs. 20.7%) OS rates (*p* = 0.011).

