*Randomized Controlled Multicenter Study* ● Signed and dated informed consent form. ● 18 years of age and older. ● Diagnosis of unresectable Stage 3 pancreatic adenocarcinoma cancer cytologically or pathologically confirmed per American Joint Committee on Cancer (AJCC) staging criteria. ● Tumor evaluated as Stage 3 according to National Comprehensive Cancer Network (NCCN) guidelines, based on radiographic imaging or exploratory surgery. ● Maximum axial and anterior to posterior tumor dimension of ≤3.5 cm, after receiving three months of treatment with the mFOLFIRINOX regimen. ● Has received 3 months of treatment with the mFOLFIRINOX regimen. ● Has an Eastern Cooperative Oncology Group (ECOG) performance status of 0 or 1. ● Has an American Society of Anesthesiologists (ASA) classification of physical health status of 1, 2, 3 or 4.	*Multicenter Registry* ● Signed and dated informed consent form ● 18 years of age and older ● Diagnosis of Stage 3 PC cytologically or pathologically confirmed per American Joint Committee on Cancer (AJCC) staging criteria. ● Tumor evaluated as Stage 3 according to National Comprehensive Cancer Network (NCCN) guidelines, based on radiographic imaging or exploratory surgery ● Maximum axial and anterior to posterior tumor dimension of ≤3.5 cm after standard of care. ● Has received 3 months of standard of care per each participating institution’s guidelines ● Has an Eastern Cooperative Oncology Group (ECOG) performance status of 0 or 1. ● Has an American Society of Anesthesiologists (ASA) classification of physical health status of 1, 2, 3 or 4. ● Are at an IRE site and are deemed eligible for IRE and receive ablation using the NanoKnife System. ● Shows no evidence of disease progression based on NCCN guidelines after completing 3 months of standard of care.
Key Exclusion Criteria	

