#### Sample size and statistical considerations

### Randomized controlled trial

Randomization will be conducted centrally. Concurrent randomization to either the IRE or control arm will take place at the completion of 3-month modified FOLFIRINOX administration, at participating sites, and be stratified by the response following 3 months of treatment with mFOLFIRINOX (responder vs. stable disease), planned type of IRE procedure (open or percutaneous) and planned post-procedure treatment (chemotherapy versus radiotherapy/ chemotherapy versus observation). A total of 444 Intent-to-treat population (ITT) subjects (with 222 subjects in each arm) are required for at least 80% power for the primary efficacy endpoint (OS), with the expectation that there will be a total of 380 events in both arms. With the consideration of up to 16% attrition rate in both arms, and assuming a median survival of 12 months and exponential survival, up to 528 subjects (with 264 subjects per arm) will need to be randomized.

The sample size consideration for the primary endpoint OS was based on the assumptions that 1) there will be a 1:1 randomization scheme, 2) median survival will be 12 months and 16 months in the control and the IRE arm, respectively, i.e., a hazard ratio of 0.75 for IRE versus control 3) there will be a 5% 2-sided type I error, 4) there will be an accrual period of 36 months and follow-up period of 24 months after the study is fully enrolled. In addition, based on an assumption that median times to PFS will be 6 months and 8 months in the control and IRE arm, respectively, the study has at least 80% power for analysis of the difference in the secondary endpoint of time to PFS between the IRE and control arms.

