For the secondary efficacy analysis, the null hypothesis for PFS is H_0_: μ_control_ = μ_IRE_ with the alternative hypothesis being H_1_: μ_control_ ≠ μ_IRE_,where μ_control_ is the median PFS time for the control arm, and μ_IRE_ is the median PFS time for the IRE arm. This study is powered to show the superiority of PFS of 2 months in the IRE arm over the control arm. The above null hypothesis will be tested by a 2-sided log rank test at 0.05 significance level only if the result of testing the primary efficacy endpoint is statistically significant. If the above null hypothesis is rejected by the two-sided test and the observed median PFS time in the IRE is greater than in the control arm, the alternative hypothesis will be established and the superiority of the PFS in the IRE arm will be statistically proven.

Analysis of the primary efficacy endpoint and key secondary endpoints will also be performed for the mITT population as supportive analyses. Safety analysis will be performed on the Safety population. To control the overall type I error rate for testing efficacy endpoints, a fixed-sequence testing procedure will be used to test the primary and secondary efficacy endpoints in a predefined order. The test will be performed in sequence and significance of OS endpoint is required in order to proceed to the testing of PFS endpoint. All statistical tests will be at the two-sided 0.05 significance level and the corresponding *p*-values and 95% confidence intervals (CIs) will be reported. Subjects alive or lost to follow-up at the time of analysis will be censored at their last date of follow-up. In the final analysis, OS will be compared between the randomized treatment arms using a two-sided log-rank test at a type I error rate of 0.05. ITT analysis will be the primary analytic methods, supported with mITT and Cox proportional hazards analysis. Kaplan-Meier methods will be used to summarize survival distribution of OS and median OS time for each treatment arm. The relative treatment effect between the IRE arm and the control arm with respect to OS will be estimated by the hazard ratio (HR) and the associated two-sided 95% CIs using the Cox proportional hazards model.

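### The stated overall survival test in the randomized trial uses no covariates; pre-specifying tumor size, known at entry, would gain a little power, roughly 0 to 3.5 points

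*Protocol article*

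**What the plan says.** Under Statistical analysis, Randomized controlled trial, the protocol article sets the deciding OS test: "OS will be compared between the randomized treatment arms using a two-sided log-rank test at a type I error rate of 0.05". It then adds: "ITT analysis will be the primary analytic methods, supported with mITT and Cox proportional hazards analysis". The Cox model supplies the hazard ratio and its confidence interval, and PFS is to be handled similarly. No stratum or covariate is named for any of these. For the registry study, by contrast, the article does say that the log-rank test is stratified, by propensity score quintiles.

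Under Sample size and statistical considerations, the trial's randomization strata are response to induction, planned open or percutaneous procedure, and planned post-procedure treatment. Tumor size is not among them.

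The Background treats size as prognostic. In general terms: "The probability of survival is inversely proportional to tumor size". From a 50-patient retrospective review of percutaneous IRE it reports that "patients with tumors ≤3 cm had significantly longer median OS than patients with tumors > 3 cm", with medians of 33.8 and 22.7 months from diagnosis and 16.2 and 9.9 months from IRE.

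Table 1 makes size an entry criterion: "Maximum axial and anterior to posterior tumor dimension of ≤3.5 cm, after receiving three months of treatment with the mFOLFIRINOX regimen".

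**The concern.** A log-rank test that ignores a prognostic factor pulls the estimated hazard ratio toward 1 and loses some power compared with a test that accounts for it. It also leaves chance imbalance in that factor uncorrected. Here the factor is measured before randomization in everyone, and the article itself cites it as related to survival.

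The OS design has almost no reserve: its calculated power is 80.07% against a target of at least 80%. A non-significant OS result also closes the fixed sequence before PFS is tested. Adjustment chosen after the data are seen would carry little weight, so the choice has to be made in advance.

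**Working it through.** **1. The plan's own figures.** The inputs, from the sample size section, are "there will be a 5% 2-sided type I error", "median survival will be 12 months and 16 months in the control and the IRE arm, respectively, i.e., a hazard ratio of 0.75", 1:1 allocation, 80% power, 36 months of accrual and 24 months of further follow-up.

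- Deaths (Schoenfeld): 4 × (1.960 + 0.842)² / (ln 0.75)² = 4 × 7.849 / 0.08276 = 379.4, so 380. The plan says 380. (Freedman's formula gives 385.)
- Power at 380 deaths: Φ(½√380 × 0.2877 − 1.960) = Φ(0.844) = 80.07%.
- Subjects: with uniform accrual and exponential survival, P(death) = 1 − (e^(−24λ) − e^(−60λ)) / (36λ), where λ = ln 2 / median. With 222 per arm this gives 198.6 + 182.3 = 380.9 deaths. The plan says 444 subjects for 380 deaths.
- Attrition: 444 / 0.84 = 528.6. The plan says 528.

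The stated design reproduces.

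**2. Size effect.** Under exponential survival the ratio of medians gives the hazard ratio for above 3 cm versus up to 3 cm: 33.8 / 22.7 = 1.49 from diagnosis and 16.2 / 9.9 = 1.64 from IRE. Because of the 3.5 cm cap, a weaker value of 1.25 was also taken (assumption). The share of subjects above 3 cm is not given; 10% to 50% was assumed.

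**3. Simulation.** Settings: 444 subjects, analysis at the 380th death, control median 12 months, treatment hazard ratio 0.75 within each size group, and no interaction between size and treatment. There were 10,000 trials per setting (20,000 for the 1.25 rows). The table shows power for the unadjusted log-rank and for the log-rank stratified by size.

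| Size HR | Share above 3 cm | Unadjusted % | Stratified % | Gain (points) |
|---|---|---|---|---|
| 1.25 | 10% | 78.8 | 78.8 | 0.0 |
| 1.25 | 20% | 79.8 | 79.8 | 0.0 |
| 1.25 | 35% | 79.1 | 79.2 | 0.2 |
| 1.25 | 50% | 79.0 | 79.4 | 0.4 |
| 1.49 | 10% | 78.95 | 79.28 | 0.3 |
| 1.49 | 20% | 78.63 | 79.98 | 1.4 |
| 1.49 | 35% | 77.28 | 78.93 | 1.7 |
| 1.49 | 50% | 77.37 | 79.19 | 1.8 |
| 1.64 | 10% | 78.78 | 79.53 | 0.8 |
| 1.64 | 20% | 77.73 | 79.72 | 2.0 |
| 1.64 | 35% | 76.41 | 78.65 | 2.2 |
| 1.64 | 50% | 76.82 | 79.90 | 3.1 |

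Simulation error is about ±0.8 points on each power figure from 10,000 trials, and less on the paired gain. A separate run of 4,000 trials at 1.64 and 50% gave 75.9% and 79.3%, a gain of 3.4 points. The range is therefore roughly 0 to 3.5.

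With no size effect at all, the unadjusted test reached 79.4-79.5% in 4,000 trials per setting. A little of each gap to 80% therefore comes from the Schoenfeld approximation and not from size.

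**4. Validity.** With no treatment effect (size HR 1.64, 50% above 3 cm), the two-sided rejection rate was 5.2% unadjusted and 5.3% stratified.

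**5. What a gain is worth.** For the unadjusted test, 81% power needs 390 deaths and 83% needs 411. One to three points therefore equal 10 to 31 deaths beyond 380.

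**6. Chance imbalance.** With 222 per arm and 35% above 3 cm (assumed), the 95% range of the between-arm difference is ±1.96 × √(2 × 0.35 × 0.65 / 222) = ±8.9 percentage points. Multiplied by ln 1.49 to ln 1.64, that shifts the log hazard ratio by about 0.035 to 0.044. This is 0.34 to 0.43 of its standard error, 2/√380 = 0.103.

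**The case against.** The strongest objection is that nothing here is wrong. An intention-to-treat log-rank is a standard primary test, its type I error holds, and the sample size was built for it. This stands, and it makes the point an efficiency suggestion.

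Second, strata and Cox covariates are often left to a statistical analysis plan, which is not shown. This stands in part: that plan may already adjust for size. But the article states the deciding test without strata, while it does name strata for the registry test. Size is also absent from the listed randomization factors. Recommending one specific covariate is more than asking for detail.

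Third, a reader might infer that size is strongly prognostic among the subjects who will be enrolled. The documents do not support that. The figures come from one 50-patient retrospective review of IRE-treated patients, and the article gives no upper size limit for its group above 3 cm. Here that group can only span 3.0 to 3.5 cm after induction. One of the two contrasts is also timed from diagnosis, whereas trial OS runs from randomization.

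Fourth, the gain is not wholly free. Stratifying on a factor with no effect lost about 0.4 to 0.5 points in 4,000 trials per setting, and adjustment requires a choice of covariate form. An adjusted hazard ratio also answers a slightly different question from the marginal one.

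Finally, adjusting only the supportive Cox model would not change the power of the log-rank that decides superiority. That is correct, and the fix takes it into account.

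**Conclusion.** The point holds as a minor, optional improvement. Adjusting the OS analysis for tumor size would gain roughly 0 to 3.5 points of power at 380 deaths, probably toward the low end. The gain is near zero if few subjects exceed 3 cm or if the size hazard ratio is about 1.25.

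This rests on exponential survival, proportional hazards, no interaction between size and treatment, a treatment hazard ratio of 0.75 within size groups, and the assumed share and effect of larger tumors. The simulation stratified by size alone; it did not model the randomization factors.

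Two stronger readings are not supported. A reader might infer that the trial is underpowered or its test invalid, but 380 deaths, 444 subjects and 80% power reproduce and type I error stays near 5%. A reader might also infer that the registry's propensity model omits size, but the article lists no propensity covariates, so nothing shows whether size is in or out.

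**What to change.** Before any unblinded analysis, and so before the interim look at about 251 deaths, pre-specify tumor size at randomization, preferably continuous, together with the three randomization factors in the Cox models that give the reported OS and PFS hazard ratios and confidence intervals.

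That alone improves the estimate but not the deciding test. To obtain the power gain there too, make the matching adjusted or stratified test primary, use the same test at the interim and final analyses, and keep the unadjusted log-rank as a sensitivity analysis. If the test is stratified, watch for sparse cells: the randomization factors alone give 2 × 2 × 3 = 12 cells, and splitting size at 3 cm makes 24, or 444 / 24 = 18.5 subjects per cell on average. A covariate-adjusted test with continuous size avoids this.

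If the analysis plan already does this, no change is needed. Otherwise the cost is a few sentences of wording, with no new data, visits or subjects.

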#### Study endpoints and assessments

The primary efficacy endpoint for both the RCT and the registry study will be OS defined as the time (in months) from randomization or enrollment in the registry to the date of death for any reason. Co-primary safety endpoints include time (in months) from randomization or enrollment in the registry to death or new onset of Grade 4 AE, and the development of high-grade complications defined as any AE or SAE with a CTCAE v5.0 grade of 3 or higher.

Secondary endpoints for both studies include a) PFS defined as the time (in months) from randomization or enrollment in the registry to the date of first observed disease progression (per clinical and radiologic criteria), or death from any cause, if death occurs without documented disease progression, b) procedure-related pain in subjects in the IRE arm, as measured by the Brief Pain Inventory (BPI-SHORT FORM) on the day of the procedure and post-procedure days 1, 7, 14 and 30, c) cancer-related pain assessed in the control and IRE arms using the BPI-SHORT FORM at baseline, 3 months, 6 months and at 6-month intervals thereafter, and d) QOL assessed in the control and IRE arms using the EQ-5D questionnaire at baseline, 3 months, 6 months and then at 6-month intervals for the duration of the study.

The registry study will also assess several exploratory endpoints including chemotherapy-free days (after 3 months of SOC), the need for opioids for cancer-related pain, OS from date of pancreatic cancer diagnosis, PFS from date of enrollment, and identification of risk factors and biomarkers associated with outcomes. Additional QOL exploratory endpoints which will be collected include rates of avoidable events associate with chemotherapy in the IRE arm during chemotherapy free days compared to the control arm, unplanned readmissions within 30 days following discharge, and in-hospital mortality.

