Subjects who do not have disease progression and have not died, will be censored at the date of last tumor assessment. Subjects with a single missing radiologic or clinical assessment immediately prior to a visit with documented disease progression (or death) will be analyzed as a PFS event at the time of the clinical or radiologic assessment that shows progression. Subjects with two or more consecutive missing radiologic or clinical assessments immediately prior to an assessment without documented progression (or death) will be censored at the date of last assessment when the subject was documented as progression-free prior to the first of the two or more missing assessments. PFS will be analyzed using similar statistical methods as that for the OS endpoint.

Pain Severity Scores and average Pain Interference Score will be derived for each subject from BPI-SHORT FORM questionnaire. QOL measures will be derived for each subject from the EQ-5D questionnaire, including the EQ Visual Analogue Scale (VAS) and EQ-5D summary index. Both absolute change and percent change from baseline will be analyzed by treatment arm and by study visit for all of the above.

For the primary safety endpoints, a log-rank test will be used to compare the time (in months) from randomization to death or new onset of Grade 4 AEs for the two treatment arms, with data censored at the time of loss to follow up or study discontinuation. The number and proportion of subjects with a high-grade complication defined as any AEs or SAEs with a CTCAEv5.0 grade of 3 or higher will be summarized by treatment arm and CTCAE grade.

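### The RCT's PFS rule for two or more missed assessments is printed for subjects who return without progression, which contradicts the general censoring rule beside it; the word is probably a slip

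*Protocol article*

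**What the plan says.** The Protocol article sets three PFS rules in one paragraph (Statistical analysis, Randomized controlled trial):

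1. General rule: "Subjects who do not have disease progression and have not died, will be censored at the date of last tumor assessment".
2. One missed assessment: subjects with "a single missing radiologic or clinical assessment immediately prior to a visit with documented disease progression (or death") count as a PFS event at the assessment that shows progression.
3. Two or more missed: the trigger and its consequence read "two or more consecutive missing radiologic or clinical assessments immediately prior to an assessment without documented progression (or death) will be censored". The censoring date is that of the last assessment at which such subjects were "documented as progression-free prior to the first of the two or more missing assessments".

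The definition under Study endpoints and assessments counts first observed progression, "or death from any cause, if death occurs without documented disease progression". It sets no limit on the time since the previous assessment.

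PFS is the secondary endpoint in the RCT's fixed testing sequence and is tested only if OS is significant. The sample-size section assumes that "median times to PFS will be 6 months and 8 months in the control and IRE arm, respectively" and states that "the study has at least 80% power for analysis of the difference in the secondary endpoint of time to PFS".

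**The concern.** Rules 2 and 3 look like a pair, one missed assessment against two or more, but their triggers are opposite. Rule 2 starts from a visit with progression or death. Rule 3 starts from an assessment without it.

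As printed, rule 3 acts on subjects for whom no censoring is needed: a clean assessment after the gap shows that no progression was missed. Rules 1 and 3 then give such a subject two different censoring dates. If the subject progresses or dies later, rule 3 removes an event that was observed.

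The situation such a rule normally addresses, progression first seen directly after a long gap, has no rule of its own.

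At stake are the event and censoring dates of the only secondary endpoint in the fixed sequence, in an unblinded trial. Those dates should not depend on how a programmer later reconciles two sentences.

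**Working it through.** **1. The plan's own figures.** Inputs from Sample size and statistical considerations (RCT): OS medians 12 and 16 months and PFS medians 6 and 8 months (HR 0.75 for both), two-sided alpha 0.05, 1:1 allocation, 36 months' accrual plus 24 months' follow-up, 444 subjects (528 with attrition).

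- Events for 80% power (Schoenfeld): 4 × (1.960 + 0.842)² / (ln 0.75)² ≈ 380, as stated.
- Event probability with exponential times and uniform accrual: p = 1 − [exp(−24λ) − exp(−60λ)] / (36λ), with λ = ln 2 / median. For PFS this gives 0.985 (control) and 0.962 (IRE).
- Expected PFS events: 222 × (0.985 + 0.962) ≈ 432 of 444, or 264 × (0.985 + 0.962) ≈ 514 of 528.
- Power = Φ(√d × |ln 0.75| / 2 − 1.96): 84.9% for 432 events and 90.3% for 514.

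The stated PFS power of at least 80% reproduces. The problem is in the derivation rule, not in the sample size.

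**2. The rules side by side.** Illustration with assumed visits at months 3, 6, 9, 12 and 15. The subject is progression-free at month 3 and misses months 6 and 9.

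| What follows | General rule or PFS definition | Rule 3 as printed | Rule 3 with *with* for *without* |
|---|---|---|---|
| Clean at 12, nothing later | censored at 12 | censored at 3 | censored at 12 |
| Clean at 12, progression at 15 | event at 15 | censored at 3 | event at 15 |
| Progression at 12 | event at 12 | not covered, so event at 12 by default | censored at 3 |

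Row 1 is the direct contradiction. Row 2 is the lost event. In row 3, a gap of any length gives an event by default, so limiting rule 2 to a single missed assessment has no effect. That is the main sign that *with* was meant.

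**3. Size, on assumptions.** The article gives neither an assessment schedule nor a missed-visit rate. Assumed: exponential PFS (6 and 8 months) and each visit missed independently with probability 10%, 20% or 30%.

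*444 subjects, 3-monthly visits:*

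| Missed | Censored back by printed rule | Progression first seen after a gap of two or more | Events, printed rule | Events, reworded rule |
|---|---|---|---|---|
| 10% | about 1% | about 2% | 424 | 420 |
| 20% | about 5% | about 8% | 412 | 396 |
| 30% | about 9% | about 16% | 397 | 357 |

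*528 subjects, 2- or 3-monthly visits, 20% of PFS events being deaths:* the printed rule censors 1.1% to 13.5% of control and 1.6% to 18.9% of IRE subjects early. The IRE share is higher in every scenario (for example 10.2% versus 7.0% with 2-monthly visits and 20% missed). Subjects who stay progression-free longer have more chances of a gap followed by a clean assessment.

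*Hazard ratio, printed rule against the PFS definition:* a shift of about 0.00-0.02 with equal missingness. With 10% missed in one arm and 20% in the other it is about 0.02-0.04, towards the null if IRE misses more and away from it if control does.

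*Power at HR 0.75:* with 528 subjects, events run from 436 to 506 (printed) and 430 to 503 (reworded), so power is about 85% or more. With 444 subjects and 3-monthly visits, the printed rule gives 84%, 83% and 82%, and the reworded rule 84%, 82% and 78%. With 2-monthly visits and 30% missed, scaling 436 events to 444 subjects gives 436 × 444 / 528 ≈ 367 and about 79% for the printed rule.

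**The case against.** The strongest reply is that this is a one-word slip in a journal overview and that the full protocol or analysis plan may state the rule correctly. The slip is likely, and the operative text cannot be checked here. That lowers the severity. But the article states the rule in full and in conflict with its neighbour, so the published sentence needs correcting either way.

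Rule 3 could also be defended as a deliberate exception that overrides the general rule. It would still throw away a clean assessment and every later event, and the article gives no reason for that.

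Three stronger readings are tempting and are not supported:

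- *Progression or death after a long gap is wrongly dated.* The paragraph does not address progression in that situation. It becomes an event only by default, through the PFS definition. Counting such events is a legitimate convention, and a death date does not depend on the assessment schedule.
- *Death after a gap has no rule at all.* The words in brackets in rule 3 can be read two ways: an assessment showing neither progression nor death, or else a death. On the second reading, deaths after a gap are censored. Rule 2 favours the first. On either reading, returning progression-free subjects are censored early and progression after a gap is not covered.
- *The PFS comparison is seriously biased.* The calculated shifts are modest, and the larger ones need unequal missed visits that the article does not report. The reworded rule is not free of this either: it moved the hazard ratio by up to about 0.02 in the unequal scenarios.

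**Conclusion.** The point holds as a wording error in an operative rule. Followed as printed, the rule gives wrong PFS times for subjects who return progression-free after two or more missed assessments, contradicts the general censoring rule and drops later observed events. *Without* for *with* is the probable cause.

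The effect is small to moderate: about 1% to 9% of subjects censored back with 3-monthly visits and 10% to 30% missed, more with 2-monthly visits, and a hazard-ratio shift of at most about 0.04. All of this rests on assumed schedules and random missed visits.

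A reader might infer that the trial's main result or its power is in doubt. It is not. OS, the sample size and alpha are untouched, PFS is tested only after OS succeeds, and the stated PFS power reproduces. Power dips just below 80% only if 30% of visits are missed and only 444 subjects contribute. This should be fixed, but it is not critical.

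**What to change.** - Reword rule 3 so that its trigger is an assessment *with* documented progression or death directly after two or more missed assessments, if that is what was intended, with censoring at the last progression-free assessment before the gap.
- State explicitly whether a death after such a gap is censored or counted.
- State that subjects who return progression-free stay at risk and follow the general rule.
- Add one sensitivity analysis that counts every progression and death regardless of missed visits, in line with the PFS definition.

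The cost is one reworded sentence, two clarifications and one analysis, settled before PFS is derived. In most assumed scenarios the reworded rule also yields fewer events than the printed one (420/396/357 against 424/412/397 above), because it censors observed progressions and deaths. It can itself shift the hazard ratio slightly when the arms miss visits unequally. That is the reason for the sensitivity analysis.
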